## Abstract

**Background:**

Simulation as a pedagogical approach has been used in health professional education to address the need to safely develop effective clinical skills prior to undertaking clinical practice. However, evidence for the use of simulation in midwifery is largely anecdotal, and research evaluating the effectiveness of different levels of simulation fidelity are lacking.

Woman centred care is a core premise of the midwifery profession and describes the behaviours of an individual midwife who demonstrates safe and effective care of the individual woman. Woman centred care occurs when the midwife modifies the care to ensure the needs of each individual woman are respected and addressed. However, a review of the literature demonstrates an absence of a valid and reliable tool to measure the development of woman centred care behaviours. This study aims to determine which level of fidelity in simulated learning experiences provides the most effective learning outcomes in the development of woman centred clinical assessment behaviors and skills in student midwives.

**Methods/Design:**

Three-arm, randomised, intervention trial.

In this research we plan to:

a) trial three levels of simulation fidelity - low, medium and progressive, on student midwives performing the procedure of vaginal examination;

b) measure clinical assessment skills using the Global Rating Scale (GRS) and Integrated Procedural Performance Instrument (IPPI); and

c) pilot the newly developed Woman Centred Care Scale (WCCS) to measure clinical behaviors related to Woman-Centredness.

**Discussion:**

This project aims to enhance knowledge in relation to the appropriate levels of fidelity in simulation that yield the best educational outcomes for the development of woman centred clinical assessment in student midwives. The outcomes of this project may contribute to improved woman centred clinical assessment for student midwives, and more broadly influence decision making regarding education resource allocation for maternity simulation.

## Background

### Woman centred care in midwifery

Midwifery is as much an art as it is a science [1]. Whilst the development of proficient psychomotor technical skills is critical for safe midwifery practice [2], equally important is the development of non-technical skills. These non-technical skills include proficiency in global clinical performance, communication, documentation and, essential to midwifery practice, an acknowledgement that pregnancy and birth is woman centred. Woman centred care is practiced in such a way that it values, supports and respects the woman, her ideas, questions, preferences, choices and decisions. Woman centred care is effected in an environment of shared power and responsibility between the woman and her midwife [3,4]. Woman centred care in clinical assessment is safe, supportive, and gentle. Woman centred care is an art that is handed down from one generation of midwives to another, the foundations of which are embedded in undergraduate midwifery courses, and strengthened through shared experiences in clinical practice [4].

### Simulation in the midwifery context

Simulation has been a key educational technique in medical and nursing training [5] in which elements of the real world are appropriately integrated to learning. Midwifery education has employed simulation methodology since the 1700’s when Madame de Coudray, a royal midwife, was commissioned by King Louis XV to travel and teach student midwives and used life size models of women she made from leather, bones and fabric [6]. In the following centuries, torso models and manikins were used to teach midwifery clinical skills such as abdominal palpation, mechanisms of labor and neonatal resuscitation.

### Simulation fidelity in the midwifery context

Simulation techniques vary in their levels of fidelity or realism and this is not dependent upon the level of technology. High fidelity may be achieved through low technology simulations and conversely the use of high technology simulators does not guarantee high fidelity. Simulation fidelity varies in midwifery education including the use of scenarios, peer-to-peer learning, partial task trainers, computerized task trainers, screen based simulations, virtual reality, haptic systems, standardized patients and full scale simulation and is used extensively in Australian midwifery programs to teach both technical and non-technical skills [7].

A study by McKenna et al. [8], looked at the perceptions of Australian midwifery educational leaders, who believed simulation could offer educational opportunities to support the development of competent midwives as long as the realism of the equipment was appropriate. This study recommended further investigation regarding the effect of differing levels of simulation fidelity on educational outcomes to ensure the most appropriate use of limited resources.

Recently simulation has been used to address the need to develop clinical skills prior to clinical practice to ensure patient safety, enhance clinical confidence prior to clinical exposure and reduce pressure on over-worked clinical environments [5,9]. Despite this change in educational methodology, minimal documentation regarding the effectiveness of these educational methods exists, including the effect on the development of woman centred care skills in student midwives.

In our study high fidelity will be achieved using simulated standardized patients, whom are individuals trained to act as a real patient to simulate a set of symptoms or problems [10]. Medium fidelity will be achieved using part-task trainers in combination with an innovative hybrid standardized patient in the format of a life size poster of a pregnant woman known affectionately as ‘Flat Maggie’. ‘Flat Maggie’ was developed internally by [name] and [name], as a visual simulation of a pregnant woman in order to increase the realism of the learning experience. Low fidelity will be achieved by the use of part-task trainer only.

### Wom*a*n centred care vs. wom*e*n centred care

Within the literature a great deal is written about the primacy of woman centred care in the practice of midwifery [3,4,11-15]. The concept of woman centred care is central to midwifery practice and underpins the philosophy statement of the International Confederation of Midwives [13] and the Australian College of Midwives [14]. Debate exists around wom***e***n centred care and wom***a***n centred care with the former relating to institutional or organisational practices that cater for particular groups of women and the later to practices demonstrated by the individual midwife that cater for an individual woman [4]. Regardless, to promote the safe and effective care of women and families, the development of woman centred care behaviours are essential for student midwives to care for women in a holistic manner.

### Measuring midwifery skills

A variety of tools exist to measure development of task-based skills in health care professionals, including the Global Rating Scale (GRS) for the evaluation of technical skills [16] and the Integrated Procedural Performance Instrument (IPPI) [17]. A useful framework for assessing the development of practice behaviours in student midwives is the Australian Nursing and Midwifery Council National Competency Standards for the Midwife [18]. However, a review of the literature demonstrates the absence of a valid and reliable tool to measure the development of woman centred care behaviours. So piloting a tool to measure woman centred care behaviours is an important secondary aim in this research. These essential woman centred care behaviours are seen as integral in any midwifery care episode and therefore should be embedded, developed and assessed as part of the education of student midwives.

A proposed conceptual framework for woman centred care comprises eight key concepts which have been identified and defined [4,19,20]. These concepts have subsequently been linked to competencies, elements and cues from the National Competency Standards for the Midwife [18] and translation into practice behaviors identified and described. For example in the Woman centred care scale (WCCS) under the construct of Midwife /Mother relationship, the student performing the procedure will need to demonstrate skills in accurately interpreting the woman’s sensory cues during the procedure and demonstrating compassionate responses to performing care in order achieve a strongly agree standard on the tool. These practice behaviours can be directly linked the National Competency standards for the Midwife 2.1 and 3.3 [18]. These eight key identified and defined concepts of midwifery care form the basis of the tool to assess performance of woman centred care behaviours during practice of clinical technical skills. Further details of the development, content validation and refinement of this tool will be reported elsewhere.

### Aim(s) of the study

This research aims to determine the effect of progressive simulation fidelity on the development of global and integrated technical skills and woman centred clinical assessent skills in student midwives. The primary aim is to determine which level of fidelity of simulated learning experiences (low, medium or progressive fidelity) provides the most effective learning outcomes. The secondary aim of this study is to pilot a tool for assessing woman centred care behaviors in undergraduate midwifery students.

### Research question

Which level of fidelity of simulated learning experiences contributes to better global, integrated and woman centred care clinical assessment in student midwives?

### Hypotheses

#### Primary hypotheses

1. Students who undertake progressive fidelity experience will demonstrate higher Global Rating Scale (GRS) scores than students who undertake lower fidelity experience.

2. Students who undertake progressive fidelity experience will achieve higher Integrated Procedural Performance Instrument (IPPI) scores than students who undertake lower fidelity experience.

#### Secondary hypotheses

1. Students who undertake medium fidelity experience will demonstrate similar Woman Centred Care Scale (WCCS) scores as those that have progressive fidelity experience.

2. Students who undertake progressive fidelity experience will achieve higher Woman Centred Care Scale (WCCS) scores than students who undertake lower fidelity experience.

## Methods/Design

The three arm intervention trial replicates the methodology employed in a study evaluating the effectiveness of progressive fidelity in the acquisition of Intravenous cannulation technical and non-technical skills in medical students [21].

### Sample & intervention

In our study, first year Bachelor of Midwifery (BM) and Dual Degree (DD) Bachelor of Nursing and Bachelor of Midwifery students from the University of Queensland (UQ), who have yet to receive theoretical instruction on vaginal examination will be recruited. Following random allocation via a computer generated block randomization schedule, participants will be assigned to one of three intervention arms. The participants will receive identical theoretical instruction in the performance of vaginal examination. All participants will be provided with a list of process goals, including woman centred care behaviours developed from published guidelines and will be briefed on the nature and expectations of the simulation experience by a simulation expert.

Senior Bachelor of Midwifery (BM) and Dual Degree (DD) Bachelor of Nursing and Bachelor of Midwifery students (3rd year or 4th year students respectively) will be recruited to act in the role of the standardized patient. These students will be provided with training and scripts to be followed as standardized patients and will be briefed on the nature and expectations of the experience by the simulation expert. The standard scenario, including all associated history, details and expected responses to questions, will be developed by the group participating as standardized patients, guided by the simulation expert.

To achieve similar statistical significance demonstrated in the Brydges et al. [21] methodology it was determined that;

#### Intervention arm 1

Intervention Arm 1 (n = 35) will receive **low fidelity** skills training using a **partial task trainer** positioned on a standard hospital birth-suite bed. Partial task trainers are designed to replicate a part of a system or process, in this research, Model-Med Charlie Obstetric Trainer® is used (Figure 1).

**Figure 1 F1:**
[figure not shown]
**Intervention arm 1.** Low fidelity will be achieved by the use of part-task trainer only, for the clinical procedure.

#### Intervention arm 2

Intervention Arm 2 (n = 35) will receive **medium fidelity** skills training using the same **partial task trainer** as provided in Intervention Arm 1, but with the addition of a ‘Flat Maggie’ positioned on a standard hospital birth-suite bed. ‘Flat Maggie’ will be draped over pillows in a bed to visually simulate a pregnant woman and the partial task trainer will be appropriately positioned in relation to the ‘Flat Maggie’ for the skill to be practiced (Figure 2).

**Figure 2 F2:**
[figure not shown]
**Intervention arm 2.** Medium fidelity will be achieved using part-task trainers in combination with an innovative hybrid standardized patient in the format of a life size poster of a pregnant woman known affectionately as ‘Flat Maggie’.

#### Intervention arm 3

Intervention Arm 3 (n = 35) will receive **progressive fidelity** skills training through **low** – **partial task trainers**, **medium** – ‘**Flat Maggie’ with the partial-task trainer**, and then to **high fidelity – Standardized patients with the partial-task trainer** positioned on a standard hospital birth-suite bed. Standardized patients will be senior midwifery students who act the part of the pregnant woman, using a consistent and standard approach. It is important to note that standardized patients **will not** be subject to vaginal examination, rather they will act the role of the woman and a partial task trainer will be appropriately positioned for the skill to be performed (Figure 3).

**Figure 3 F3:**
[figure not shown]
**Intervention arm 3.** High fidelity will be achieved using simulated standardized patients who are final year midwifery students trained to act as a real patient to simulate a set of symptoms or problems, with an appropriately positioned partial task trainer.

### Sample size and statistical power

To ensure that the type I error rate for the entire study is 0.05, the sample size calculations used a type I error rate of 0.025 (Bonferroni’s correction) to account for the two primary outcome measure; GRS and IPPI scores.

#### GRS

Based on data from Brydges et al. [21], the expected sample standard deviation to be used in the sample size calculation was 3.6. Along with this parameter, a power of 80%, type I error of 0.025, and the assumption that the average GRS scores in the progressive, medium and low fidelity groups will be 11, 10 and 8, 102 participants are required. Inter-rater reliability (intraclass correlation = 0.76) and internal consistency (Cronbach’s alpha = 0.75) of the GRS have been demonstrated in published research studies [22].

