#### IPPI

Based on data from Brydges et al [21], the expected sample standard deviation to be used in the sample size calculation was 18. Along with this parameter, a power of 80%, type I error of 0.025, and the assumption that the average IPPI scores in the progressive, medium and low fidelity groups will be 40, 33 and 25, 105 participants are required. Validation of the IPPI has been demonstrated in previous research studies; a recent study reported inter-rater reliability (intraclass correlation = 0.73), internal consistency (Cronbach’s alpha = 0.65) and discriminant validity (p < 0.001) [22].

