### Statistical methods

The descriptive characteristics of each of the three groups will be presented; continuous characteristics will first be assessed for distribution using histograms and the Shapiro-Wilk test. If the data is normally distributed, the mean and standard deviation will be presented, and for data that is not normally distributed, the median and interquartile range will be reported. Numbers and percentages will be used for categorical data. Comparison of the primary outcome measure amongst the three groups will be undertaken using either analysis of variance (ANOVA) or Kruskal-Wallis testing, dependent on the distribution of the outcome. If a statistically significant difference is found (at the 0.025 level), appropriate post-hoc testing will be conducted to determine which groups are different.

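### The 80% power is for the three-group overall test: it carries over to progressive versus low fidelity, but not to progressive versus medium, which the primary aim also needs

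*Protocol article*

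**What the plan says.** All references are to the Protocol article.

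- **Aim(s) of the study:** "The primary aim is to determine which level of fidelity of simulated learning experiences (low, medium or progressive fidelity) provides the most effective learning outcomes".
- **Primary hypotheses:** the first reads "Students who undertake progressive fidelity experience will demonstrate higher Global Rating Scale (GRS) scores than students who undertake lower fidelity experience". The second makes the same directional claim for the IPPI. Neither says whether lower fidelity means the low arm, the medium arm or both.
- **Sample size and statistical power:** alpha is halved to 0.025 for each of the two primary outcomes. The GRS calculation uses SD 3.6, "a power of 80%, type I error of 0.025", and the assumption that "average GRS scores in the progressive, medium and low fidelity groups will be 11, 10 and 8, 102 participants are required". The IPPI calculation uses SD 18 and the assumption that "average IPPI scores in the progressive, medium and low fidelity groups will be 40, 33 and 25, 105 participants are required". The trial takes 105, that is 35 per arm. No pairwise power is given.
- **Statistical methods:** the three groups are compared by ANOVA or Kruskal-Wallis, depending on distribution. Then: "If a statistically significant difference is found (at the 0.025 level), appropriate post-hoc testing will be conducted to determine which groups are different".

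**The concern.** A significant overall test says only that the three means are not all equal. It does not say that progressive is higher, or which level is best. Those answers come from the pairwise step, for which the article gives no power, so the question is how far the 80% carries over to it.

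The stake is the comparison of progressive with medium. The Discussion says that the results may influence how education resources are allocated, and what progressive adds to medium includes the stage with standardized patients. If that comparison has little power, the likeliest pattern is that progressive beats low while progressive versus medium is not significant. If the protocol does not say that this contrast is weakly powered, the result could be taken to mean that medium does as well, although the sample size itself assumes that it does not.

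**Working it through.** **Inputs (GRS, IPPI and WCCS subsections).** GRS: SD 3.6; means 11, 10, 8 (progressive, medium, low). IPPI: SD 18; means 40, 33, 25. Alpha 0.025 per outcome; 35 per arm.

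**1. Reproduce the stated totals.** For the one-way F test with n per arm, λ = n·Σ(μᵢ − μ̄)²/SD², with 2 and 3(n − 1) degrees of freedom.
- GRS: μ̄ = 9.667 and Σ(μᵢ − μ̄)² = 4.667. At n = 34, λ = 34 × 4.667/12.96 = 12.24 and power is 81.2%; n = 33 gives 79.8%. Total 3 × 34 = 102, as stated.
- IPPI: μ̄ = 32.667 and Σ(μᵢ − μ̄)² = 112.67. At n = 35, λ = 35 × 112.67/324 = 12.17 and power is 81.0%; n = 34 gives 79.6%. Total 3 × 35 = 105, as stated.

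At 35 per arm the overall test has 82.5% (GRS) and 81.0% (IPPI) power.

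**2. Single contrasts at 35 per arm.** Noncentral t with 102 df, noncentrality δ = (d/SD)·√(35/2), two-sided 0.025, critical value 2.275.

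| Contrast | d/SD | δ | Power |
|---|---|---|---|
| Progressive vs low, GRS | 3/3.6 = 0.833 | 3.49 | 88.5% |
| Progressive vs low, IPPI | 15/18 = 0.833 | 3.49 | 88.5% |
| Progressive vs medium, GRS | 1/3.6 = 0.278 | 1.16 | 13.7% |
| Progressive vs medium, IPPI | 7/18 = 0.389 | 1.63 | 26.3% |

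**3. The planned route: post-hoc tests only after a significant F.** The article names no post-hoc method, so a range is shown, from Tukey at 0.025 to unadjusted tests at 0.025 (200,000 simulated trials per outcome).

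| Contrast | GRS | IPPI |
|---|---|---|
| Progressive vs low | 78.5–81.5% | 78.3–80.5% |
| Progressive vs medium | 7.2–13.5% | 15.7–25.9% |
| Medium vs low | 37.5–51.0% | 22.0–33.6% |

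The power to show progressive better than both other arms is 7–13% (GRS) and 15–26% (IPPI).

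**4. Sensitivity to sidedness.** The article does not state it. One-sided 0.025 for progressive versus medium gives about 21% (GRS) and 36% (IPPI), still far below 80%.

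**5. Size needed.** For 80% power on progressive versus medium at two-sided 0.025, about 248 (GRS) or 127 (IPPI) per arm would be required, against 35.

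**6. What a non-significant result could exclude.** With the planned SDs, the half-width of a 97.5% confidence interval for a pairwise difference is 2.275 × SD × √(2/35): 1.96 points for the GRS and 9.8 for the IPPI. Both exceed the assumed progressive–medium differences of 1 and 7, so such a result could not establish that the two are equal.

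**The case against.** The strongest case on the other side has four parts.

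- **Nothing is miscalculated.** The totals match the test that Statistical methods plans, at the stated alpha, and no passage claims 80% power for a pairwise contrast. This stands.
- **The primary hypotheses can be read as adequately powered.** The secondary hypotheses expect medium to be similar to progressive on the WCCS and, beside that, progressive to be higher than lower fidelity. If lower fidelity included medium, the two would conflict, so it most naturally means the low arm. On that reading the primary hypotheses concern a contrast with about 78–88% power. This stands too. A reader might infer that the 80% holds for the overall test alone, or that every post-hoc comparison is underpowered; the article's own figures do not support either reading.
- **Overall test then post-hoc is standard.** With three groups under ANOVA, even unadjusted pairwise tests after a significant F hold the error rate for each outcome, and the name of the post-hoc method can be left to a fuller document. Agreed; neither is criticised here.
- **No passage says that a non-significant difference on the GRS or IPPI will be read as equality.** True. The only hypothesis of similarity concerns the piloted WCCS. The misreading is a risk to guard against, not something that the article commits to.

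What remains is the aim. It covers all three levels and so needs progressive compared with medium, whatever lower fidelity means, and the article does not say that this comparison is weakly powered.

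**Conclusion.** The point holds in a limited form. The totals of 102 and 105 are right for the overall test. The 80% carries over, nearly or fully, to progressive versus low: 78–81% by the planned route and 88.5% as a planned contrast. It does not carry over to progressive versus medium, at about 7–14% (GRS) and 16–26% (IPPI), and therefore not to the aim of identifying the best of three levels.

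A second consequence concerns efficiency. Testing progressive versus low directly raises its power by about 7 to 10 percentage points at the same sample size and alpha.

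These figures rest on the article's assumed means and SDs, normal outcomes, a common SD, 35 analysed per arm and two-sided tests. They do not describe the Kruskal-Wallis branch. This should be fixed, but it does not invalidate the design.

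**What to change.** 1. **Primary hypotheses:** define lower fidelity as the low-fidelity arm, consistent with the secondary hypotheses.
2. **Statistical methods:** for each primary outcome, make progressive versus low a planned contrast from the one-way model at two-sided 0.025. Test progressive versus medium at the same level only if the first is significant; the fixed order keeps the error rate for each outcome at 0.025. If the outcome is non-normal, use a rank-based pairwise test in the same order. Report medium versus low as an estimate with a confidence interval, outside the sequence.
3. **Sample size (GRS, IPPI and the closing total):** state that 80% refers to the overall test, that progressive versus low has about 88% power, and that progressive versus medium has about 14% (GRS) and 26% (IPPI). State that a non-significant progressive–medium result will not be read as equivalence.

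**Cost:** wording only, with no extra participants. Medium versus low is no longer formally tested; the power given up there is 37–51% (GRS) and 22–34% (IPPI) under the present route. The change does not make progressive versus medium adequately powered. It only discloses how weak that comparison is, and the stated power becomes much less favourable.
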